##### Antioxidant status

We hypothesize that the oxidative stress associated with prematurity will be diminished with oropharyngeal administration of OMM, as measured by changes in levels of validated urinary biomarkers of oxidative stress, and this will correlate with the development of L-OS (late onset sepsis) and NEC (necrotizing enterocolitis).

Extremely premature infants are predisposed to oxidative stress-derived diseases because of (1) the need for oxygen supplementation in the first weeks of life with an overproduction of highly reactive oxygen-derived free radicals (FR) capable of causing damage to DNA, proteins and lipids; (2) immaturity of the antioxidant enzymatic and non-enzymatic defense system [83–89]. The deleterious action of free radicals upon proteins, lipids, and DNA can be assessed by determining highly specific biomarkers using ultra high performance liquid chromatography coupled to tandem mass spectrometry (UPLC-MS/MS) methods that have been validated using Food and Drug Administration (FDA) stringent requirements.

Our hypothesis is based on previous observations by our research team ([name]) showing that human milk-fed preterm infants have better antioxidant capacity compared to formula-fed cohorts [87]. [name] has established normative ranges for the measurement by UPLC-MS/MS of urinary biomarkers in extremely premature infants reflecting oxidative damage to proteins [87, 88]. His research has validated the whole spectrum of metabolites derived from phenylalanine (Phe) oxidation by non-physiologic pathways (orto, meta, nitro, 3Chlor-tyrosines) and oxidative damage to guanidine bases of DNA (8-oxo-dihydroxi-guanosine), and non-cyclo-oxygenase (COX) derived oxidative byproducts of arachidonic and docosahexanoic acid, essential components of cell membranes, in extremely premature infants such as F2-isoprostanes, specific Prostaglandins (PGs), Isofurans (IsoFs), Neuroprostanes (NeuPs) and Neurofurans (NeuFs).

The approach used to test this hypothesis will be the PGs and isoprostanes (IsoPs) in urine samples of the first 50 (25 milk, 25 placebo) enrolled infants, collected at 4 time points as depicted in Fig. 2. UPLC-MS/MS analysis is carried out on an Acquity-Xevo TQ system (Waters, Milford, MA, USA) using negative electrospray ionization. MS/MS detection is carried out by multiple reaction monitoring (MRM) employing specific acquisition parameters. In milk-treated infants, we anticipate lower elimination of oxidized tyrosines, oxidized bases of DNA and IsoPs and PGs compared to baseline. We expect urinary metabolites of the placebo-treated infants to be within the established ranges for the different metabolites.

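### For the exploratory oxidative-stress aim (2B), the only comparisons the article names are not between the randomised arms, and its predictions cover markers outside the measurement it names

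*Protocol article*

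**What the plan says.** The hypothesis in the Antioxidant status section is causal: "the oxidative stress associated with prematurity will be diminished with oropharyngeal administration of OMM". The section then describes how it will be examined: "The approach used to test this hypothesis will be the PGs and isoprostanes (IsoPs) in urine samples of the first 50 (25 milk, 25 placebo" infants), with urine taken at four time points. The Study design section gives these as baseline, the end of the 48-hour initial period, 7 days of life, and the end of the extended period at 32 weeks corrected gestational age.

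Two expected results follow. For the milk arm: "In milk-treated infants, we anticipate lower elimination of oxidized tyrosines, oxidized bases of DNA and IsoPs and PGs compared to baseline". For the placebo arm: "We expect urinary metabolites of the placebo-treated infants to be within the established ranges for the different metabolites".

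No milk-versus-placebo contrast is named for these markers. The neighbouring Lactoferrin section does name one for the other urinary marker, a mixed-effects model asking whether levels or changes over time differ between the two groups. The article labels Aim 2 as a whole exploratory.

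**The concern.** A claim that milk lowers oxidative stress needs the milk arm set against the placebo arm. Here each arm has its own yardstick: its own starting value for milk, an external range for placebo. If the markers drift downward as infants mature, the milk arm falls below baseline whether or not milk does anything, and a placebo arm that falls equally can still sit inside a normative range. Both expectations would then be met with a true effect of zero.

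The article gives a reason to consider such drift. It ties oxidative stress to oxygen need in the first weeks and to immature antioxidant defences, and the last urine sample comes at 32 weeks corrected age.

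A second mismatch concerns the markers. The named measurement is prostaglandins and isoprostanes, but the prediction extends to oxidised tyrosines and oxidised DNA bases. A reader cannot tell whether results on protein and DNA oxidation are to be expected.

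At stake is the interpretation of one exploratory mechanism, not the efficacy result.

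**Working it through.** **The plan's own figures.** The sub-study states no effect size, SD, alpha or power, so there is nothing to reproduce beyond 25 + 25 = 50, which is consistent.

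**Part 1: can both expectations hold with no effect?** Let both arms fall by the same amount.
- Milk against its own baseline: lower, so the expectation is met.
- Placebo against the established range: can still be inside, so the expectation is met.
- Milk against placebo: difference zero.

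This needs no numbers. It needs only that a shared fall occurs.

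**Part 2: how often would a within-arm test mislead?** The article specifies no such test. This calculation applies only if one were used.

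Inputs: n = 25 milk infants (Antioxidant status section). Assumed: paired t test, two-sided alpha 0.05, no treatment effect, a shared fall of s SD between baseline and follow-up, and baseline/follow-up correlation r from 0.3 to 0.7.

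Standardised change: d = s / √(2(1 − r)). Noncentrality: d × √25 = 5d. Critical value: t(0.975, 24 df) = 2.064.

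Worked example, s = 0.5 and r = 0.5: d = 0.5 / √1 = 0.50; noncentrality 2.5; probability of significance 0.67.

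| Assumed fall | r = 0.3 | r = 0.5 | r = 0.7 |
|---|---|---|---|
| 0 SD | 5% | 5% | 5% |
| 0.2 SD | 13% | 16% | 24% |
| 0.5 SD | 53% | 67% | 87% |
| 0.8 SD | 90% | 97% | 99.9% |

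A simulation (40,000 runs, falls of 0 to 0.8 in units of the SD of change) agrees: a significant fall in the milk arm in 16% of runs at 0.2 and 97% at 0.8. In the same runs a two-sample test of change, 25 v 25, stayed at about 5% whatever the shared fall.

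**Part 3: what the between-arm comparison can detect.** Two-sample t test, 25 per arm, two-sided alpha 0.05, 80% power: 0.81 SD. Adjusting for baseline at r = 0.5 multiplies this by √(1 − 0.5²) = 0.866, so 0.81 × 0.866 = 0.70 SD.

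**Part 4: marker lists side by side.**

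| Marker class | Named as test measurement | Fall predicted |
|---|---|---|
| Prostaglandins | yes | yes |
| Isoprostanes | yes | yes |
| Oxidised tyrosines | no | yes |
| Oxidised DNA bases | no | yes |

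Two of the four predicted classes lie outside the named measurement. The section says assays for them were validated in earlier work; it does not say they will be run in this trial.

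**The case against.** The strongest reply is that the two sentences are forecasts. They say what the investigators anticipate and expect; they set no test, no alpha and no rule for calling Aim 2B supported. That stands. A reader might infer that the trial will declare Aim 2B supported on a within-arm fall, or that it discards the randomisation of the 50 infants. The document supports neither inference. Both arms are sampled in equal numbers at the same time points, which points towards a comparison of arms, and a fuller protocol or analysis plan may state one.

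It is also fair that the article gives no time course, direction or size for maturational change. Treatment starts within 96 hours of birth, and the samples after the initial period and at 7 days still fall in the early weeks when oxygen need is a cause of stress. Only the 32-week sample clearly fits the maturation argument. So a fall from baseline without any effect is possible, but the document does not establish that it is expected.

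On the markers, a reader might conclude that tyrosine and DNA-base results would have no data behind them. That goes too far. The section describes the same mass-spectrometry platform as able to assess protein, lipid and DNA damage, so the named list may simply be incomplete.

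The reply does not remove the point that, directly after introducing how the hypothesis will be tested, the article names two comparisons and neither can answer it. This is not only a matter of detail left elsewhere: the comparisons printed are the wrong ones, while the next section prints the right kind for lactoferrin.

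**Conclusion.** The point holds in limited form. As written, the comparisons named for Aim 2B cannot separate a milk effect from a change shared by both arms, and the predicted markers exceed the named measurement. The first follows from the text together with the possibility of a shared fall; the second follows from the text alone.

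The error rates are conditional. They assume a within-arm paired test that the article does not specify, and a fall whose size it does not give. Across the assumed falls and correlations they run from 5% to nearly 100%, so they illustrate the risk and do not estimate it.

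Severity is minor. The aim is exploratory, and nothing here touches late-onset sepsis, necrotising enterocolitis, death, safety or the sample size.

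**What to change.** In the Antioxidant status section, state that Aim 2B is tested by milk versus placebo at the post-baseline time points, adjusted for the infant's own baseline value, using a mixed model of the kind given for lactoferrin. Keep change from baseline and comparison with established ranges as description only.

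Make the marker list consistent: either limit the predictions to prostaglandins and isoprostanes, or state that oxidised tyrosines and DNA bases are measured in the same urine.

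The first change is wording only; infants, samples and planned assays stay as they are. The second is also wording only if the predictions are trimmed, or if the additional markers were already to be measured; otherwise it adds assay work. The price is a more demanding test: as computed above, 25 v 25 reaches 80% power only for differences of about 0.7 to 0.8 SD, so the result may look less favourable. If a between-arm analysis was always intended, saying so costs nothing.

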##### Lactoferrin

We hypothesize that oropharyngeal administration of OMM will be associated with higher concentrations of urinary lactoferrin in treated infants. Our hypothesis is based on our pilot data [70], which showed higher concentrations of urinary lactoferrin in infants who received oropharyngeal administration of mother’s colostrum, compared to placebo-treated controls. No significant between-group differences were found; however, the sample size was small (*n* = 16). A large effect size (1.30) was noted for urinary lactoferrin, which suggests that results may have reached statistical significance if a larger sample had been used. This finding is consistent with research that has shown higher concentrations of urinary lactoferrin in mother’s milk-fed infants compared to formula-fed cohorts [90, 91]. Further studies have shown that the urinary lactoferrin is of maternal origin [92–94], although the precise mechanism of entry into the urine is unknown. The approach used to test this hypothesis will be the measurement of lactoferrin in urine samples at 3 time points (see Fig. 2), using a commercial ELISA assay. Lactoferrin concentrations will also be measured in milk samples from mothers, at the same three time points, to clarify whether the infant’s levels are due to the milk or from neonatal immune responses resulting from other factors. A mixed-effects regression model will be applied to assess whether the average at each time point or change over time is different between the two groups. The analysis will be done first for infant and mother separately, then an index variable will be created to define mother versus infant, and the difference between mothers and infants will be assessed. Appropriate variance-covariance structure will be determined by Akaike Information Criterion (AIC). Normality assumption will be evaluated using Shapiro-Wilk’s test or visualization of data distribution. Appropriate data transformation (i.e. log, square root) will be applied to correct the skewness.

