## Methods/Design

### Study design

This study is a 5-year, prospective, double-blind, placebo-controlled randomized clinical trial across 5 large neonatal centers, designed to evaluate the safety and efficacy of oropharyngeal administration of own mother's milk to reduce the incidence of L-OS, and NEC and death, in a large cohort of extremely premature infants (*n* = 622; total patients enrolled). A multi-center 5-year trial is necessary in order to reach the target sample, based on average numbers of extremely premature infants admitted yearly to participating sites. Enrolled infants are randomized to one of 2 groups using computer-generated random numbers: Group A (treatment) infants receive 0.2 mL of own mother’s milk (OMM) via oropharyngeal administration every 2 hours for an initial treatment period of 48 continuous hours, followed by an extended treatment period of 0.2 mL of OMM via oropharyngeal administration every 3 hours until 32 weeks CGA. Group B infants (control) receive a placebo (sterile water, and blinded as described below) using the same dose and following the same protocol. Samples of mother’s milk and infant’s urine are collected at baseline and within 6 hours after the completion of the Initial Treatment Period and the Extended Treatment Period. A sample of infant’s urine is collected at 7 days of life. Milk, oral mucosal swab, and stool samples are collected at the time of first stool, 2 weeks of life and at 32 weeks CGA. For infants diagnosed with L-OS or NEC, a stool sample is collected at the time of diagnosis. Health outcome and safety data are closely monitored and collected throughout the infant’s stay until discharge or death. See Fig. 1 for the timeline of the study.

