##### Analysis of safety endpoints

Safety endpoints will be analyzed using summary statistics (frequency, count, percent). We will compare each safety endpoint between milk and placebo groups using chi-square and Fisher exact tests. We will also analyze the safety endpoint count data by conducting Poisson regressions using group (milk versus placebo) as the independent variable, controlling for covariates described above if applicable.

##### Outcome measures for specific Aim 2

This is an exploratory aim of the trial and, therefore, should not be considered as the primary endpoint of the study. We hypothesize that oropharyngeal administration of OMM will modulate microbiome, antioxidant status and urinary lactoferrin concentrations for recipient infants. These measures are described below.

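### The urinary lactoferrin comparison appears to include the pre-treatment sample as a tested time point and states no baseline adjustment, so one contrast is uninformative and the others are less precise than they could be

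*Protocol article*

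**What the plan says.** The Lactoferrin section of the protocol article hypothesizes that oropharyngeal milk will be "associated with higher concentrations of urinary lactoferrin in treated infants". It plans the "measurement of lactoferrin in urine samples at 3 time points", with milk lactoferrin measured "at the same three time points". A mixed-effects regression will "assess whether the average at each time point or change over time is different between the two groups". The covariance structure is chosen by AIC, and skewed values may be transformed. The section mentions no baseline adjustment and does not say which of the listed comparisons is the main one.

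The Study design section says that milk and urine are "collected at baseline and within 6 hours after the completion of the Initial Treatment Period and the Extended Treatment Period". It adds a sample for which only "urine is collected at 7 days of life".

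The section on outcome measures for Aim 2 limits the claim: "This is an exploratory aim of the trial and, therefore, should not be considered as the primary endpoint of the study".

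**The concern.** The baseline sample precedes any study treatment. After randomization, an arm difference there can only be chance, yet the wording puts it among the comparisons of interest. The post-treatment means are then compared as if the baseline value were unknown. The change comparison does use baseline, but it subtracts the whole value whatever the correlation, which adds noise when the correlation is modest. The plan therefore collects a baseline sample and does not use it in the most efficient way. The word joining the two kinds of comparison also leaves open which result would answer the hypothesis.

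At stake is the precision and clarity of the Aim 2C mechanism finding. Nothing in the primary analysis depends on it.

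**Working it through.** **Which three time points.** Urine is listed at four times: baseline, end of Initial Treatment, end of Extended Treatment and day 7. In that schedule milk is paired with urine at the first three, and day 7 is listed for urine only. The Lactoferrin section uses three times, the same for urine and milk. Only baseline and the ends of the two treatment periods fit, so baseline is one of the compared time points. This is an inference, as Fig. 2 is not shown.

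**No planned figure to reproduce.** The article gives no alpha, power, sample size or correlation for lactoferrin. Its 498 analysed infants and two-sided 0.05 are stated for late-onset sepsis and are not used in the precision check.

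**Precision at one post-treatment visit.** Take equal variance σ² at each visit on the transformed scale, correlation ρ between baseline and that visit, and n infants per arm. The variance of the arm contrast is (2σ²/n) × k, where in large samples:
- unadjusted post-treatment mean: k = 1
- change from baseline: k = 2(1 − ρ)
- baseline as covariate: k = 1 − ρ²

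The correlation is assumed, so a range is shown.

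| ρ | Unadjusted | Change | Baseline-adjusted |
|---|---|---|---|
| 0.2 | 1 | 2 × 0.8 = 1.6 | 1 − 0.04 = 0.96 |
| 0.4 | 1 | 2 × 0.6 = 1.2 | 1 − 0.16 = 0.84 |
| 0.6 | 1 | 2 × 0.4 = 0.8 | 1 − 0.36 = 0.64 |

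Against the unadjusted mean, adjustment cuts the variance by 4% / 16% / 36%. Against change, the ratio is (1 − ρ²) / [2(1 − ρ)] = (1 + ρ)/2 = 0.6 / 0.7 / 0.8, a cut of 40% / 30% / 20%. Change is worse than the unadjusted mean whenever ρ < 0.5. The adjusted comparison is never worse than either.

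**False-positive rate under one possible reading.** Suppose that any nominal two-sided 5% result were read as an effect. Three independent tests would reject with probability 1 − 0.95³ = 14.3%. The following rates come from simulating the arm differences with no milk effect (large-sample normal, equal or first-order autoregressive correlation, ρ from 0 to 0.8):
- three time-point tests or the 2-df arm-by-time test: 15.0–15.4% for ρ from 0 to 0.5, and 13.6–14.0% at ρ = 0.8
- the same without the baseline contrast: 11.8–12.4%
- trials rejecting through the baseline contrast alone: 1.7–3.3%
- arm-by-time test alone: 4.9–5.1%
- one joint 3-df test of all arm differences: 4.8–5.1%
- two separate baseline-adjusted post-treatment tests: 8.7–9.8%
- one joint 2-df test of the baseline-adjusted post-treatment differences: 4.9–5.1%

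Most of the excess is ordinary multiplicity. Baseline adjustment without a single test would still leave about 9–10%.

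**The case against.** A reader might infer that the planned analysis produces false positives about three times as often as 5%, and that baseline imbalance is the reason. The documents do not support either step. The Lactoferrin section describes what the model will estimate. It sets no alpha and does not say that any one significant result counts. The model itself does not have a 15% error rate, since its interaction test and a joint test both hold 5%. Dropping the baseline contrast would only bring the any-result rate down to about 12%.

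The hypothesis is also directional. A pre-treatment difference, or lower lactoferrin in the milk arm, would not support it. Counting only results in milk's favour (a higher post-treatment mean, or a significant interaction with positive average change) gives about 6.3% under no effect, against 2.5% for a single test. Some multiplicity remains, but far less than the larger figure suggests.

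Three further points are fair. Keeping baseline in the response vector is a standard longitudinal model, and unadjusted post-treatment means are unbiased under randomization. Naming a main contrast for an exploratory biomarker may be left to the statistical analysis plan. Averaging the two post-treatment samples is not clearly better, because one follows 48 hours of treatment and the other is taken at 32 weeks corrected age, so an effect at only one of them would be diluted.

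These points remove any claim of a breached error rate or of bias. They do not make the baseline contrast informative, and they do not change the precision comparison, which concerns the comparisons the article itself names.

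**Conclusion.** The point holds as a modest improvement in method. On the text, the arm comparison includes a pre-treatment time point that cannot bear on the hypothesis, and the other comparisons named are less precise than a baseline-adjusted one. At one visit the variance falls by 4–36% against the unadjusted mean and by 20–40% against change, for assumed correlations of 0.2 to 0.6.

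This rests on three assumptions: that baseline is one of the three time points, equal variances across visits, and the assumed correlations. At low correlation the gain over the unadjusted mean is small. The 14–15% false-positive rate is conditional on a decision rule that the article does not state, and should not be quoted as a property of the plan. Aim 2 is exploratory, so no confirmatory error rate is at issue.

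**What to change.** In the Lactoferrin section, remove the arm contrast at baseline. Fit the mixed model to the post-treatment transformed urinary lactoferrin values with the transformed baseline value as covariate. Alternatively, keep baseline in the response and constrain both arms to a common baseline mean, which retains infants without a baseline sample. Name one joint 2-df test of the two post-treatment arm differences, or one pre-named contrast, and show visit-specific differences as estimates with confidence intervals.

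The cost is a sentence or two of analysis text and no new samples. A joint test is less sensitive than an averaged contrast when the effect is the same at both visits, while an averaged contrast dilutes an effect confined to one. That choice should be made before the data are seen.

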With oropharyngeal administration, milk drops are placed directly onto the infant’s oral mucosa [66, 69], so that biofactors may provide immunostimulatory effects [66–70]. Using this approach, we theorize that oropharyngeal administration of own mother's milk is protective against L-OS and NEC [48] via several mechanisms: 1) interaction of milk cytokines with oropharyngeal immune cells, 2) mucosal absorption of protective biofactors, 3) barrier protection against pathogens, 4) local and systemic effects of oligosaccharides which modulate intestinal microbiota and 5) beneficial effect of protective antioxidants. Milk cytokine interaction with OFALT may provide immune stimulation. Mucosal absorption of (milk) lactoferrin may result in higher concentrations of urinary lactoferrin suggestive of systemic immune protection against L-OS. A recent small (*n* = 48) RCT [71], which was designed to determine the immunologic effect of oropharyngeal colostrum administration, showed higher concentrations of urinary lactoferrin for milk-treated extremely premature infants at 1 week of age, compared to placebo-treated controls (3.5 versus 0.9 μg/g creatinine *P* = 0.01). This finding is consistent with our own pilot data [70], and suggests that lactoferrin may be absorbed via the mucosa with passage into the circulation, and then excreted into urine following oropharyngeal milk therapy [71]. During oropharyngeal administration of mother’s milk, intestinal growth factors may also be absorbed mucosally or may travel to the gut and accelerate intestinal maturation. Oligosaccharides may be absorbed mucosally with systemic effects, or may travel to the gut where they can exert prebiotic effects enhancing *Bifidobacteria* spp. growth, and also serve as decoy receptors to competitively bind and inhibit pathogens, preventing translocation and L-OS. Barrier protection (provided by lactoferrin and secretory immunoglobulin A) prevents pathogen adherence to epithelial cell surfaces in the gastrointestinal tract, protecting against both L-OS and NEC. Antioxidants protect immune cells from injury, prevent oxidative stress-induced changes in microbiota which promote pathogenic species and thereby reduce inflammation and injury to the intestinal epithelium, preventing translocation and protecting against L-OS and NEC. Milk macrophages may also travel to the gut, where they can survive for up to a week and secrete intestinal growth factors and anti-inflammatory cytokines [63].

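### The planned mother-versus-infant lactoferrin contrast compares milk with urine and cannot serve its stated purpose of showing whether infant urinary lactoferrin comes from the milk

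*Protocol article*

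**What the plan says.** The Lactoferrin section of the protocol article plans "measurement of lactoferrin in urine samples at 3 time points" in infants. It adds: "Lactoferrin concentrations will also be measured in milk samples from mothers, at the same three time points". The milk assay has a stated purpose, which is to clarify whether the infant's "levels are due to the milk or from neonatal immune responses resulting from other factors".

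The analysis has two steps. First, "A mixed-effects regression model will be applied to assess whether the average at each time point or change over time is different between the two" study arms, fitted for infants and mothers separately. Second, "an index variable will be created to define mother versus infant, and the difference between mothers and infants will be assessed". The covariance structure is to be chosen by AIC, and skewed data may be transformed. No association between a mother's milk and her own infant's urine is named.

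Under the heading on outcome measures for specific Aim 2, the article states the standing of this work: "This is an exploratory aim of the trial and, therefore, should not be considered as the primary endpoint of the study".

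**The concern.** The milk samples have one declared job, which is to separate two explanations for lactoferrin in the infant's urine. The analysis assigned to them sets one fluid's level against another's. In the joint model the index variable coincides with type of fluid: every mother value is milk and every infant value is urine. A gap, or no gap, between the two fits either explanation.

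At stake is the interpretation of an exploratory mechanism aim. The milk assays at three time points would yield a contrast that does not address their purpose and could be misread as evidence on source. The paired data that bear on the question are already being collected.

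**Working it through.** The article gives no sample size, power or expected value for lactoferrin, so there is no plan figure to reproduce. The check is algebra plus a simulation on assumed inputs.

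**1. The level contrast.** Let M be a mother's milk value and U her infant's urine value on the analysis scale, with means μM and μU, standard deviations σM and σU, and within-pair correlation ρ. Then:

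- expected contrast = μM − μU, which does not contain ρ;
- variance of M − U = σM² + σU² − 2ρσMσU.

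The pairing enters only through the standard error. With assumed SD 0.8 for both and 100 pairs:

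- ρ = 0: √[(0.64 + 0.64)/100] = √0.0128 = 0.113;
- ρ = 0.6: √[(1.28 − 0.768)/100] = √0.00512 = 0.072.

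So a milk-to-urine link changes the precision of the contrast, not the quantity it estimates.

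**2. Simulation.** Assumed: 100 pairs, log scale, SD 0.8, 2,000 replicates, and mean gaps of 7, 3 and 0. Urine is either unrelated to own mother's milk (ρ = 0) or tracks it (ρ = 0.6), with the same marginal means in both cases. Each cell gives ρ = 0 / ρ = 0.6.

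| Gap | Mean difference | Contrast rejects | Urine-on-milk slope rejects |
|---|---|---|---|
| 7 | 7.00 / 7.00 | 100% / 100% | 4.9% / 100% |
| 3 | 3.00 / 3.00 | 100% / 100% | 5.0% / 100% |
| 0 | 0.00 / 0.00 | 5.1% / 5.8% | 5.4% / 100% |

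The contrast responds to the assumed gap and not to the link. The slope does the reverse.

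**3. Interaction terms.** These were not part of the simulation, but they can be reasoned through.

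- *Index by arm:* (μM − μU) in the milk arm minus (μM − μU) in the placebo arm equals the arm difference in milk minus the arm difference in urine. If randomisation leaves mothers' milk alike on average, this is just the arm effect on urine with its sign reversed, which the separate infant model already estimates.
- *Index by time:* this compares the average time course of milk with that of urine. Two averages can run in parallel because both change with postnatal age, without any infant's urine following its own mother's milk.

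Neither term links a mother to her own infant.

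**The case against.** The strongest case against the point has four parts.

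- **The sentence on assessing a difference is brief.** It could cover time courses or arm effects as well as levels. That is fair, and the simulation covers levels only. The algebra for the interaction terms shows that the wider reading does not supply the missing link. A random effect shared by mother and infant would carry some pair association in the covariance, but the plan does not make that a target of inference.
- **The hypothesis of Aim 2C is higher urinary lactoferrin in treated infants.** The randomised arm comparison tests this validly. That stands. Source attribution is ancillary to the aim, and nothing in the article makes it the key step. But the arm comparison alone cannot separate absorbed milk lactoferrin from an induced infant response, because either could raise urine levels in the milk arm. That is the question given to the milk samples.
- **A full analysis plan may add a paired analysis.** It may. The point rests on the analysis the article does state, not on missing detail.
- **A paired slope does not identify source cleanly either.** This stands. Placebo infants may also be fed their mother's milk, shared determinants such as gestational age could produce a slope, and variable absorption could flatten a real one.

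A reader might also infer more than the article supports:

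- **One variance for both fluids.** AIC selection could admit a structure that differs by fluid.
- **Urine scaled to creatinine here.** That unit belongs to the small trial cited in the Background, which "showed higher concentrations of urinary lactoferrin for milk-treated extremely premature infants at 1 week of age". The Lactoferrin section does not state it for this trial.
- **A near-certain significant result.** The article gives no milk values, and with no gap the contrast rejects at about the nominal rate.
- **A detectable correlation from the 249 per group.** That is the sample size for late-onset sepsis. The Lactoferrin section gives no number of pairs, and a simple correlation would not power a milk-by-arm interaction.

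**Conclusion.** The point holds in a limited form. The stated joint analysis does not serve its stated purpose: its estimand is a gap between two fluids, and that gap is the same whether or not urine follows own mother's milk. This follows from the algebra and does not depend on the simulated values. The simulation does assume that milk as the source shows up as a within-pair correlation (0.6 here); a weaker link would be harder to detect by any method.

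The consequence is small. The fault lies in one step of an exploratory aim. The randomised comparison of infant urinary lactoferrin, the primary endpoint and the clinical secondary endpoints are unaffected. A reader might conclude that Aim 2C as a whole is invalid, but the article does not support that.

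**What to change.** Replace the index contrast, or at least supplement it, with a mixed model that has:

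- **Outcome:** infant urinary lactoferrin, suitably transformed, with the unit stated.
- **Main terms:** own mother's milk lactoferrin at the matching time point, arm, time, and milk-by-arm interaction.
- **Random effects:** infant, and mother as well, because twins are eligible and share a mother.
- **Adjustment:** gestational age, and the percentage of feeding volume given as mother's milk, which the Statistical analysis section already records.
- **Baseline urinary lactoferrin:** either a covariate or an outcome, not both.

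Report the slope and its interaction with arm as supportive, exploratory evidence on source, not proof. Keep the separate randomised comparison as the test of the Aim 2C hypothesis. The arm coefficient in the new model should not replace it, because the feeding percentage is measured after randomisation.

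The cost is slightly more analysis work on the same samples and assays. Precision for the milk-by-arm interaction will be limited, and the report should say so.
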